### Randomization and blinding

In this study, participants will be divided into an intervention group and a control group using a block randomization method. The randomization sequence will be generated by a randomizer not involved in trial implementation and statistics with the aid of Stata software, setting a block length of 4, with the 60 participants divided into a total of 10 blocks.

The random assignment sequence and grouping results of the Stata software output will be recorded by the randomizer on paper and sealed in an opaque envelope with a number representing the order in which the participants are grouped. Envelopes will be kept by randomizer.

After the participants meet the enrollment criteria, sign the informed consent and complete the baseline data collection, the researchers will ask for a random number according to the enrollment order of the participants from randomizer, and then conduct clinical studies according to the predetermined treatment plan of each group.

Participating researchers include randomizers, therapists, assessors and statistical analysts. The study will be blinded to patients, assessors and statistical analysts. If a participant experiences a serious adverse reaction during the trial, unblinding will take place immediately. The procedure for unblinding will be the intervener explains to the trial leader the occurrence of a serious adverse reaction in the participant and requests unblinding. Data from this study will be reviewed and evaluated by the data monitoring committee (DMC), which consisted of 5–6 clinicians and statisticians independent of the sponsor and competing interests. And every three months there will be a trial monitoring by an independent clinical trial monitor.

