## Study design and methods

### Study design

This is a single-center randomized controlled trial, and participants will be assigned to receive acupuncture or sham acupuncture in a 1:1 ratio. Each participant will sign an informed consent form prior to enrollment. The protocol followed SPIRIT for TCM statement (22).

The total observation period will be 12 weeks, including an 8-week intervention period (weeks 0-8), and a 4-week follow-up period (weeks 8-12). Assessments will be conducted at baseline, week 2, week 4, week 6, week 8 and week 12. The study process is illustrated in **Figure 1**, while the schedule of enrolment, treatments, and assessments can be seen in **Table 1**.

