### Statistical considerations

#### Sample size

This trial is a pilot trial aim to preliminarily explore the possibility of acupuncture in the treatment of ADD, and to evaluate the feasibility of conducting further large-scale clinical trials to verify the efficacy of acupuncture. Moreover, the results of this trial will facilitate the calculation of an appropriate sample size for further randomized clinical trials. The minimum sample size for exploratory trials is 20 to 30 per group according to Provisions for Drug Registration in China. It is generally accepted that at least 30 participants are required for a pilot study (24). According to an estimate of the number of patients expected to participate in the trial and the minimum number of patients required to assess the practical purpose of the trial., we choose the maximum of 30 participants, and the sample size of 60 participants is determined.

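### A single fixed block length of 4 at one site weakens allocation concealment: up to an expected one third of assignments can be deduced from earlier ones

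*Protocol article*

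**What the plan says.** All references are to the Protocol article.

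- **Design.** Study design: "This is a single-center randomized controlled trial", and "participants will be assigned to receive acupuncture or sham acupuncture in a 1:1 ratio". No stratification is described, so there is one running sequence.
- **Block rule.** Randomization and blinding: the list is made in Stata, "setting a block length of 4", "with the 60 participants divided into a total of 10 blocks". No variation in length is mentioned, and nothing says that the length is withheld from staff.
- **Concealment steps.** Same section: the sequence is produced by a randomizer who takes no part in running or analysing the trial. It is placed in numbered opaque envelopes that this person keeps. After eligibility, consent and baseline data, "the researchers will ask for a random number according to the enrollment order of the participants from randomizer". The same sentence then has those researchers carry out the treatment plan of each group.
- **Blinding.** Same section: "The study will be blinded to patients, assessors and statistical analysts". Therapists are named among the participating researchers but are not on the blinded list.
- **Who treats.** Interventions: both groups are treated by a licensed acupuncturist trained on the study protocol. The intervention arm gets an acupuncture needle and the control arm a flat-tip needle. De qi is sought only in the intervention arm (Intervention group).

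**The concern.** Sealed envelopes held by an independent person protect against someone looking ahead. They do not protect against someone counting back. In a 1:1 block of 4, once two patients have gone to one arm, every remaining place in the block is fixed. The only knowledge needed is the block length and the earlier allocations in order.

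Much of that knowledge is within reach here. There is one site and one sequence. The operator must handle a different device in each arm, so will know the arm. Training on the protocol may well include the block length. Sixty patients over October 2024 to July 2025 (Participants) is 60/10 = 6 a month, slow enough to follow the order.

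Someone who can foresee the next arm can bring forward, delay or discourage an enrolment before the allocation is requested, so release after consent and baseline does not prevent it. Entry severity (HAMD-17 from 8 to below 20) and willingness to go without medication (Inclusion criteria) leave room for discretion. Any selection would fall on the between-group comparison of the primary outcome. A predictable sequence also makes it easier for blinded staff to learn allocations.

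**Working it through.** **Inputs.** N = 60 (Sample size: "the sample size of 60 participants is determined"); ratio 1:1; block length 4; stated number of blocks 10; one site, no strata.

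**1. The plan's own figure.** Number of blocks = N / length = 60/4 = 15, not 10. Ten blocks of 4 cover 10 × 4 = 40 patients. Ten blocks for 60 patients imply a length of 60/10 = 6. The stated length and count cannot both be right, so both lengths are carried through.

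**2. Assignments that are certain in advance, length 4.** A place is forced once one arm has used its quota of 2. The six equally likely orders give:

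| Order | Forced places |
|---|---|
| AABB | 2 |
| ABAB | 1 |
| ABBA | 1 |
| BAAB | 1 |
| BABA | 1 |
| BBAA | 2 |

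Mean = (2+1+1+1+1+2)/6 = 4/3 per block. Share = (4/3)/4 = 1/3. Over 15 blocks: 15 × 4/3 = 20 of 60. This is an expectation: the count is 15 + Binomial(15, 1/3), with SD √(15 × 1/3 × 2/3) = 1.8 and possible range 15 to 30.

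**3. Length 6.** With m per arm, the expected number of forced places is 2m/(m+1). Check at m = 2: 4/3, as above. At m = 3: 6/4 = 1.5 per block, share 1.5/6 = 25%, and 10 × 1.5 = 15 of 60.

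**4. Best guess, length 4.** The guesser always names the arm with more places left.
- Place 1: 1/2.
- Place 2: 2/3.
- Place 3: 1/3 × 1 + 2/3 × 1/2 = 2/3.
- Place 4: 1.

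Sum = 2.83, and 2.83/4 = 70.8%, against 50% if nothing can be inferred. For length 6, full enumeration gives 68.3%.

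**5. Effect of varying the length.** Simulation: 3,000 sequences of 60, each block size drawn with equal probability and the sequence cut at 60. The guesser knows which sizes are possible but not their order. The mixed sizes are illustrative assumptions.

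| Scheme | Certain in advance | Best guess correct |
|---|---|---|
| Fixed 4 | 33.3% | 70.8% |
| Fixed 6 | 25.0% | 68.3% |
| Mixed 4/6 | 5.5% | 69.1% |
| Mixed 2/4/6 | 4.0% | 70.1% |
| Mixed 4/6/8 | 2.4% | 67.8% |

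Mixing nearly removes certainty (5.5% of 60 is about 3 patients) but hardly changes the best guess.

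**6. Imbalance if recruitment stops mid-block.** The maximum is half the current block: 4/2 = 2 for a length of 4, and 6/2 = 3 for a length of 6.

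**The case against.** A reader might infer that concealment fails outright and that 20 allocations will be known in advance. The documents do not support that.

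- **Real safeguards are stated.** Generation is independent, the randomizer keeps the opaque envelopes, and release follows eligibility, consent and baseline. These stand. They prevent reading ahead, though not deduction.
- **The link from therapist to enrolment is not stated.** The term for those who request allocations also covers randomizers, assessors and analysts. Diagnosis is by at least two specialists (Participants), and enrolment-day scales are taken by postgraduates and psychologists (Data management and quality control), which points to people other than the acupuncturist. No passage says that therapists enrol patients or that enrolling staff see earlier allocations. A detailed division of roles may sit in the full protocol, so its absence from an article is not itself a fault. This stands, and it makes the one-third figure conditional.
- **Publication of the block length adds nothing that can be shown.** The text does not say whether the article appeared during recruitment. Protocol training is the more plausible route.
- **Emergency unblinding is a minor matter.** One revealed arm in a block of 4 moves each other place only from 1/2 to 1/3 or 2/3, and helps prediction only while that block is filling. No passage says that the trial leader enrols.
- **The consequences are limited.** This is a pilot with feasibility aims, and the primary model includes baseline values (Statistical analysis), which partly deals with measured severity. That does not cover unmeasured selection, and the trial still names an efficacy primary outcome.
- **Fixed blocks are common.** They are, so this is an avoidable weakness in a stated rule and not a mistake of principle.

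**Conclusion.** The point holds as a weakening of concealment. A single block length of 4, one unstratified sequence and an operator who can see the arm make allocations deducible from earlier ones, whatever the envelopes do.

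The size is an expected 33% of assignments certain in advance (20 of 60) at length 4, or 25% (15 of 60) if the intended length is 6. Best-guess accuracy is 70.8% or 68.3%. These are upper-end figures. They assume that someone able to influence screening or enrolment knows the length and every earlier allocation in order, which the article makes plausible but does not state. That the acupuncturist knows each arm is inferred from the devices and the blinded list. The resulting bias in the CDRS-R comparison cannot be calculated from the document.

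The contradiction between length 4 and 10 blocks is the firmer error in the same sentence. It means that the sequence specification has to be revisited anyway.

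**What to change.** When the length and number of blocks are reconciled and the sequence is generated:

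1. Use randomly varying block lengths that total 60, for example six blocks of 4 and six of 6 in random order (24 + 36 = 60).
2. Leave the lengths out of documents that site staff read. The randomizer alone holds them.
3. State that those who screen and obtain consent are not told earlier allocations and, where staffing allows, do not treat. Because best-guess accuracy stays near 69% under mixed blocks, this step matters more than the first.

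Suggested text: *Allocation will use permuted blocks of randomly varying length, totalling 60; the lengths are known only to the randomizer. Staff who screen or obtain consent will not have access to previous allocations.*

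**Cost.** A changed option in the Stata list generation and two sentences. The maximum imbalance if recruitment stops mid-block rises from 2 to 3; there is no rise if the intended length was already 6. If the list is already in use, the third step can still be adopted for the remaining patients, and the report should state the lengths actually used and who knew earlier allocations.

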**Methods:**

In this pilot randomized controlled trial, 60 participants will be randomly assigned to receive acupuncture or sham acupuncture for 8 weeks of treatment and 4 weeks of follow-up. The primary outcome will be the difference in Children’s Depression Rating Scale-revised (CDRS-R) scores at weeks 0 and 8 of treatment. Secondary outcomes will include 17-item Hamilton Depression Scale (HAMD-17) clinical score reduction rate and clinical remission rate, difference in CDRS-R scores, HAMD-17 scores, 14-item Hamilton Depression Scale (HAMD-14) scores, Pittsburgh Sleep Quality Index scale (PSQI) scores, and Columbia-Suicide Severity Rating Scale (C-SSRS) scores. All outcomes will be assessed at weeks 0, 2, 4, 6, 8 of treatment and week 12 of the follow-up period. In addition, we will assess the safety outcomes from baseline to the end of this trial and feasibility outcome after treatment.

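### The block specification is internally impossible: 10 blocks of length 4 give 40 allocations, not the stated 60

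*Protocol article*

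**What the plan says.** The section on randomization and blinding states that "participants will be divided into an intervention group and a control group using a block randomization method". An independent randomizer generates the sequence in Stata, "setting a block length of 4, with the 60 participants divided into a total of 10 blocks". The results go into numbered opaque envelopes that the randomizer keeps. A number is released in order of enrolment, once eligibility, consent and baseline data are complete.

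The target of 60 is fixed elsewhere too. The abstract's methods paragraph says that "60 participants will be randomly assigned to receive acupuncture or sham acupuncture for 8 weeks of treatment and 4 weeks of follow-up", and the participants section also gives 60. The sample size section takes 30 per group: "we choose the maximum of 30 participants, and the sample size of 60 participants is determined". Under study design, "This is a single-center randomized controlled trial" and "participants will be assigned to receive acupuncture or sham acupuncture in a 1:1 ratio". The article mentions no stratification, no varying block length and no second list.

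**The concern.** One sentence gives three numbers (participants, block length, number of blocks), and any two of them determine the third. They do not agree. This is not a detail that the article leaves to a fuller document: it states all three figures, and it contains no other description of the list.

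Two things are at stake. If the list was built exactly as described, it runs out before recruitment does, and someone has to arrange further allocations that the plan does not provide for. If it was built differently, the published account of sequence generation is wrong, and a reader cannot tell whether blocks of 4 or of 6 were used. Every between-group comparison rests on this sequence, so its description should be one that can be carried out.

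**Working it through.** **Inputs, all from the protocol article**

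- Participants to be randomised: N = 60 (abstract, participants, sample size, randomization and blinding).
- Block length: L = 4; number of blocks: B = 10 (randomization and blinding).
- Ratio 1:1, single centre, no strata stated (study design).

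**Reproducing the stated figure**

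Allocations = L × B = 4 × 10 = 40, against 60 stated. The shortfall is 60 − 40 = 20, and 20/60 = 33.3%. The figure is not reproduced.

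**Other readings tried**

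- Length 4 counted per arm, so 8 per block: 8 × 10 = 80.
- Ten blocks for each arm: 2 × 4 × 10 = 80.
- The list covers 40 and the rest allows for dropout: 40/(1 − d) = 60 requires d = 1/3. The article gives no dropout allowance, and the sentence itself spreads all 60 over the blocks.
- Separate lists by site or stratum: the trial has one centre and states no strata.

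None of these reconciles the three numbers.

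**What would be consistent**

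- Length held at 4: 60/4 = 15 blocks, 15 × 2 = 30 per arm.
- Count held at 10: 60/10 = 6 per block, 10 × 3 = 30 per arm.

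Both match 1:1 and 30 per group, so nothing in the article favours one over the other.

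**State of a literal list at its end**

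Ten complete 1:1 blocks of 4 close at 10 × 2 = 20 per arm. The list would be short, but balanced where it stops.

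**Predictability with fixed blocks of 4 (for the optional improvement)**

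There are six equally likely blocks. The positions that are certain, given the earlier ones in the same block, number:

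| Block | Determined positions |
|---|---|
| AABB | 2 |
| ABAB | 1 |
| ABBA | 1 |
| BAAB | 1 |
| BABA | 1 |
| BBAA | 2 |

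The total is 8 of 6 × 4 = 24 positions, or one third. This is a ceiling: it applies only to someone who knows every earlier allocation and where each block begins.

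A mixed list of the required size exists: 6 × 4 + 6 × 6 = 24 + 36 = 60, with 12 + 18 = 30 per arm.

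**The case against.** The best defence is that this is a reporting slip. The sentence itself speaks of dividing all 60 participants, so the intent to allocate everyone is clear, and the list in the envelopes may well hold 60 slots. That stands. It limits the consequence, but it does not make the sentence correct.

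A reader might infer that a third of participants will have no allocation. The article does not support this as a fact. It follows only if the list was generated as 10 blocks of 4, and the list itself is not shown. Nor would a short list by itself destroy balance or concealment: it would stop at 20:20, and further blocks made by the same independent randomizer in the same way would preserve both.

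A reader might also infer that the correct figure must be 15 blocks of 4. Ten blocks of 6 fits every other statement equally well.

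Finally, a reader might infer that allocation is foreseeable and that enrolment can be steered. Part of this is sound. Therapists are not among those listed as blinded and they handle visibly different needle devices, and the block length is fixed and published. But the article does not say that the therapist enrols participants or that one person treats everyone. The randomizer is independent, keeps the envelopes, and releases a number only after consent and baseline. A fixed block of 4 is a weaker choice than varying lengths, not an error. I treat it as advice only.

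It is also fair to say that the trial is a pilot without a power-based sample size, and that no analysis depends on the number of blocks. That lowers the stakes. It does not remove the need to correct the only description of sequence generation, at almost no cost.

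**Conclusion.** The point holds as an internal contradiction. Block length 4, 10 blocks and 60 participants cannot all be true: the first two give 40, a gap of 20. This rests on numbers in a single sentence and on a target repeated in three other places, and needs no outside assumption.

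The practical consequence is conditional. If the list was generated literally, it ends after slot 40 and 20 of 60 participants (33%) fall beyond it. If not, the list may be complete and the fault is confined to the published block count or block length. The article cannot settle which, so the list has to be checked and the text corrected. Predictability under fixed blocks is secondary: up to one third of allocations could be deduced by someone with full knowledge of earlier ones, and the article does not show that anyone involved in enrolment has that knowledge.

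**What to change.** **Required.** The independent randomizer checks the generated list, and the sentence is corrected to what it contains: 15 blocks of 4 or 10 blocks of 6. If it holds only 40 slots, the randomizer extends it to 60 by the same concealed method before slot 41 is needed, and the extension is documented. The cost is one corrected sentence, a check of the list and, at most, 20 further envelopes. No participants or staff are added.

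**Optional, only if the list is not yet in use.** Generate the 60 allocations from randomly ordered blocks of 4 and 6, for example six of each, with the lengths known only to the randomizer and left out of public text until recruitment ends. The cost is a new Stata run. The small downside is a slightly larger possible imbalance if recruitment stops mid-block: at most 3 within a block of 6, against 2 within a block of 4.

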### Interventions

In this trial, the needles used in intervention group will be the Tianxie medical stainless steel sterile millimeters needle device (Suzhou Tianxie Medical Equipment Co., Ltd.), which consisted of two parts, the acupuncture needle and the foam pad. Acupuncture needles have a thickness of 0.3 mm and a specification of 1 inch (1inch=25mm). In control group will be the Tianxie medical special flat-tip needle device (Suzhou Tianxie Medical Equipment Co., Ltd.), which consisted of two parts, the flat-tip needle and the foam pad. Flat-tip needles have the same thickness and specification of acupuncture needles.

The acupoints in both the intervention and control groups selected will be GV20, GV29, HT7 (bilateral), CV17, PC6 (bilateral), LR3(bilateral), SP6(bilateral). The localization of the acupoints refer to the national standard of the People’s Republic of China, “Names and Localization of Acupoints” (GB/T12346-2021). The operation methods and precautions are standardized in accordance with the “Acupuncture and Moxibustion Technical Practice Guidelines-Needling” (GB/T21709.21).

The interventions in both groups will be conducted by an acupuncturist registered as a licensed TCM practitioner with at least 3 years of clinical experience in acupuncture practice. The acupuncturist will receive training on study protocol and standard acupuncture manipulation before study initiation.

Each participant will have their treatment sheet, which will record the date they are supposed to come for treatment, whether they receive the treatment on time or not, and will be signed by both the intervener and the participant, in an attempt to improve the participants’ compliance.

### Intervention group

The patient will be asked to take a sitting position. After the acupoints are localized, the operator’s hands and acupoints will be routinely sterilized with 75% alcohol, and the acupuncture needles will be inserted into the body by piercing the foam pads, with the specific depths of the needles as follows: ①GV20: 0.5 inches of flat stabbing; ②GV29: 0.3 inches of flat stabbing; ③HT7 (bilateral): 0.3 inches of straight stabbing; ④CV17: 0.3 inches of flat stabbing; ⑤PC6 (bilateral): 0.5 inches of straight stabbing; ⑥LR3 (bilateral): 0.5 inches of straight stabbing; ⑦SP6 (bilateral): 0.8 inches of straight stabbing. All acupoints will be selected with 1-inch acupuncture needles for needling, giving small and even lifting-thrusting and twirling after needle insertion to achieve the effect of “De qi”, which will be defined as local soreness and distension. After that, the needles will be left in place for 20 minutes. Frequency is 2 times a week for 8 weeks of treatment.

### Control group

The patient will be asked to take a sitting position. After the acupoints are localized, the operator’s hands and acupoints will be routinely sterilized with 75% alcohol, and select 1-inch special flat-tip needles (see **Figure 2** for details) to pierce the foam pads, with the tip of the needle against the skin of the acupoint through the base of the needling device. Giving small and even lifting-thrusting and twirling after needle insertion and the needles will be left in place for 20 minutes like the intervention group. Frequency is 2 times a week for 8 weeks of treatment.

